### 5.8.5 Study Follow-up procedures

All the participating women will be given a study calling card with a 24 hour number to call and be encouraged to report any adverse events experienced to the research team, who have the responsibility to ensure that such adverse events are appropriately managed and details of the event recorded.

In the event of a problem thought by the participant to be related to the contraceptive method, routine assessment, counselling and management will be offered according to the national contraception guidelines. Strategies to manage possible side-effects without method change will be explored. In the event of discontinuation of either method, alternative choices will be offered to participants according to national contraception guidelines.

Participants will be followed at month 6 and month 6, 7days, and pending funding 12 and 18 months. Participants will receive appropriate compensation for their time and costs for in-person visits (R250 for study visits and R100 for contraception-only visits). Every attempt will be made to contact participants who do not return for follow up including repeated calls to participant's and alternative phone numbers, and where possible home visits (provided consented to). At each contact, participants will be asked to confirm their physical address and description of where they live, as well as at least one contact number for a family member or friend that they will inform about the study and are happy to have contacted by the study team. At scheduled and unscheduled visits, the women will receive free routine clinical care and referral as needed. All participants will have access to the national HIV screening and treatment programme and STI treatment through their local clinics. If any incidental health problems are detected, the women will be referred to the relevant health facilities.

---

**Table 2: Study follow-up activities(Every 6months)**

---

| Activities | Staff |
|------------|-------|
|------------|-------|

|                                                      |                       |
|------------------------------------------------------|-----------------------|
| HIV counselling and test – [30min]                   |                       |
| Locator information (update)                         | Counselor             |
| Clinical interview (CRF2) - [30min]                  | Clinician/Study Nurse |
| Antropometric measures (weight) (CRF3) - [10min]     | Clinician/Study Nurse |
| Clinical assessment (CRF3) - [30min]                 | Clinician/Study Nurse |
| BDI-II & ASEX - [15min]                              | Counselor             |
| Blood and genital tract sample collection* - [10min] | Study nurse           |

Total duration of visit not more than 2 hours.

The following data will be collected at baseline, Month 6, Month 6, 7 days, Month 7.

- Age (at baseline only)
- Previous pregnancies, whether the pregnancy was intended or unintended, and the outcome of the pregnancy (at baseline only)
- Menstruation (heavy/mod/light/none) and symptoms eg pain
- Subjective concern about weight
- Feeling sad or depressed for no real reason
- "In the last 2 weeks have you felt unable to stop worrying, or thinking too much?"
- "In the last 2 weeks have you felt down, depressed or hopeless?"
- "In the last 2 weeks have you had thoughts and plans to harm yourself or commit suicide?"
- Current contraception, date of NET or DMPA injections (confirmed from patient-held family planning record if received outside the study site)
- Reason for discontinuation of allocated method
- Frequency of condom use (always/sometimes/never/not applicable)
- Number of sexual partners in previous 3 months

## Immunological studies

The following sentinel tests are under consideration:

- CR5 levels on T cells and CD14+ cells from cytobrush sample
- plasma interferon  $\gamma$

#### **5.8.6 Contraceptive follow-up after final research visit**

At the final research visit, the women will be re-counselled about their future contraceptive choices. Any who wish to switch methods will have the option to do so. Further contraceptive care will be provided within the routine provincial health services.

#### **5.9 Criteria for discontinuation of a participant**

Participants who decline to remain in the study will be discontinued. Stopping or changing the allocated method will not be a reason for discontinuation, as analysis will be by intention to treat. Pregnancy or HIV sero-conversion will not be a reason for discontinuation, as other outcomes will remain relevant.

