#### **4. Study outcomes:**

##### **4.1 Primary outcomes**

The primary hormonal outcome will be serum 17 $\beta$  estradiol, and the primary psychological outcome will be depression (BDI-II). The study will be powered to measure a difference of 35 pmol/L in the mean serum 17 $\beta$  estradiol between arms, and a difference of 2 in the mean depression scores (BDI-II). The other measures will be regarded as exploratory.

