## 5.6 Sample size calculation

Primary psychological outcome: Depression

In our previous study, 24 MADRS scores in women randomized to NET-EN were 8.3 (standard deviation 7.5). Based on this standard deviation, to show a difference of 2 between the study groups with 95% certainty and 80% power would require 221 participants per group, and allowing for 15% loss to follow-up, 260 per group. (<http://pharmaschool.co/size4.asp>).

Primary biological outcome: serum 17 $\beta$  estradiol

In our previous study, 17 $\beta$  estradiol levels in women randomized to NET-EN were 136 pmol/L (standard deviation 119). Based on this standard deviation, to show a difference of 35 pmol/L in either direction between groups with 95% certainty and 80% power would require 181 participants per group, and allowing for 15% loss to follow-up, 213 per group (<http://pharmaschool.co/size4.asp>).

Because of multiple outcomes to be measured, the remaining outcome comparisons will be regarded as exploratory. In general, studies of biomarkers such as immune effects have used considerably smaller sample sizes.

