### 5.8.4 Follow-up visits

All participants will be asked to attend the research sites at the time of their repeat injections (2- or 3-monthly). At the 6-month and month6, 7days visit they will have blood drawn, urine and genital tract samples collected for biomarker studies and archiving. At the 6, and pending funding 12 and 18 month visits they will be offered an HIV test by study staff according to national guidelines, and a dried blood spot will be archived.

At 12 to 18 months, participants will be seen at the research site for a final dried blood spot collection and urine pregnancy test. At the end of the study, the last blood spot available will be tested for HIV by PCR. For participants with positive final HIV PCR, the baseline archived blood spots will be tested for HIV to to exclude window period infections at baseline. In the

event of failure to collect or loss of a PCR result, the relevant rapid test result will be used. In the event of discordance between PCR and rapid test results, the PCR result will be used. In the case of a positive PCR after completion of the study, the participant will be notified by the study staff.

Women who are unable to come to the research site for their final visit will have the option of an outreach visit from study personnel to perform HIV testing.

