### **8.2 Data analysis plan**

Analysis will be by intention to treat, and the results will be reported according to the CONSORT guidelines. Baseline characteristics will be compared to confirm the effectiveness of the

randomization process. Numbers and baseline characteristics of losses to follow-up will be compared between groups to detect any imbalances in loss to follow-up. Number of subjects, number of missing values and percentages will be reported for categorical variables. Number of subjects, number of missing values, minima, maxima, means and standard deviations will be reported for continuous variables. Appropriate transformation of non-normal or skewed measurement will be performed on continuous variables. If transformations do not generate a distribution approaching normality, medians and IQR will be reported.

For incidence outcomes (eg pregnancy and HIV seroconversion) with varying duration of follow up between groups, data will be adjusted for duration of follow up.

Categorical variables will be compared as risk ratios with 95% confidence intervals. For continuous data, mean differences with 95% confidence intervals will be reported.

The primary analysis will be based on all subjects with outcome data available. A sensitivity analysis will be performed that only analyzes participants who have neither discontinued nor switched contraceptive methods to assess the impact of switching and discontinuation.

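### Hormone samples drawn during pregnancy go into the primary estradiol comparison, with no rule for them and no month-6 pregnancy test to find them

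*Protocol*

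**What the plan says.** Section 4.1 makes serum 17β-estradiol the primary hormonal outcome; section 4.2 lists progesterone, sex hormone binding globulin (SHBG), testosterone and free testosterone as secondary. Section 5.6 plans estradiol as a raw mean difference: "to show a difference of 35 pmol/L in either direction between groups with 95% certainty and 80% power would require 181 participants per group".

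On women who conceive, section 5.9 says: "Pregnancy or HIV sero-conversion will not be a reason for discontinuation, as other outcomes will remain relevant". On the analysis set, section 8.2 says: "The primary analysis will be based on all subjects with outcome data available". The same section calls for intention to treat, mean differences with 95% confidence intervals, transformation of skewed measurements, and medians with IQR if transformation fails. Its one sensitivity analysis drops women who stopped or switched method; pregnancy is not mentioned.

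At month 6 and 7 days later, section 5.8.4 says "they will have blood drawn, urine and genital tract samples collected for biomarker studies and archiving". The only urine pregnancy test it schedules after enrolment is at 12 to 18 months, and section 5 makes follow-up beyond 7 months depend on funding. Table 2 lists no pregnancy test. Section 5.7.2 has women who are late for an injection assessed for pregnancy before the next one.

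**The concern.** Estradiol measured during pregnancy reflects the pregnancy, not NET-EN or DMPA. The same holds for progesterone and SHBG. The reason section 5.9 gives for retention is that other outcomes stay relevant, which leaves the primary hormonal outcome unaddressed. Read with section 8.2, the effect is that any such sample is analysed as an ordinary treatment response.

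The situation is foreseeable. The background in section 1 says nearly half of injectable users stop within 12 months and links this to high rates of unintended pregnancy. Section 5.9 also keeps women who stop the method. A woman who has stopped is not due another injection, so the late-attender check need not reach her, and her sample would not be recognised for what it is.

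At stake is whether the difference in arm means, in pmol/L, can be interpreted as a contrast between two contraceptives, and whether the trial keeps its planned power for that outcome.

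**Working it through.** **Inputs from section 5.6.** Mean 136 and SD 119 pmol/L; target difference 35; two-sided 5%; 80% power; 181 evaluable per group. The depression outcome sets the trial size: "would require 221 participants per group, and allowing for 15% loss to follow-up, 260 per group". So 221 evaluable per group is the planning figure for estradiol too.

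**The plan's own figure.** n = 2 × (1.96 + 0.842)² × 119² / 35² ≈ 181.5 per group, against 181 stated; 181 / 0.85 = 213 after loss to follow-up. These agree. At 221 per group, SE = 119 × √(2/221) = 11.32, 35 / 11.32 = 3.09, and power is about 87%.

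**Assumption.** The protocol gives no estradiol level in pregnancy. X is taken over 2,000 to 20,000 pmol/L.

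**Effect of one value X on an arm of 221 (raw scale).**
- Shift of the mean = (X − 136)/221.
- SD² = [119² × 219 + (220/221)(X − 136)²]/220.

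| X (pmol/L) | Shift of mean | Arm SD |
|---|---|---|
| 2,000 | 8.4 | 173 |
| 5,000 | 22.0 | 348 |
| 10,000 | 44.6 | 674 |
| 20,000 | 89.9 | 1,341 |

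The shift equals 35 at X = 136 + 35 × 221 = 7,871 (or 136 + 35 × 181 = 6,471 with 181 per arm).

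**Power, raw scale.** The value changes both the difference and its SE, so power was simulated: arm means 136 and 101, SD 119, 221 per arm, unequal-variance t-test, one pregnancy value.

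| X (pmol/L) | In lower-mean arm | In higher-mean arm |
|---|---|---|
| none | 87% | 87% |
| 2,000 | 44% | 92% |
| 5,000 | near 0% | about 77% |
| 8,000 | near 0% | about 40% |
| 20,000 | near 0% | near 0% |

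**False positives, raw scale.** With no true difference and one pregnancy, the rejection rate is about 5% at 2,000, about 1% at 5,000 and near 0% at 10,000. With two pregnancies in the same arm it is about 9%, 3% and near 0%.

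**Log scale.** Lognormal data with the same means and CV 119/136 = 0.875 (log SD 0.754) give about 98% power with no pregnancy. One pregnancy at 2,000 to 20,000 leaves about 96 to 99%. Three in the lower-mean arm leave about 93% at 2,000, falling to about 80% at 20,000: a loss of roughly 5 to 19 points.

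**How likely is at least one?** The protocol gives no pregnancy rate. If 0.25%, 0.5% or 1% of the 442 sampled women (2 × 221) were pregnant at month 6, the chance of at least one is 1 − (1 − p)^442 = 67%, 89% or 99%.

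**The case against.** The best defence has four parts.

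- **Retention is correct.** Section 5.9 is about staying in the study, and intention to treat supports it. This stands in full; the gap is the missing rule for the hormone samples.
- **Section 8.2 requires skewed data to be transformed.** An SD nearly as large as the mean already suggests skew, and on a log scale one pregnancy does little damage. This stands as mitigation only. The scale is not fixed in advance, the powered target and the reported measure are in raw pmol/L, and the fallback merely reports medians and IQR. A log also reduces a pregnancy value's leverage without making it a measure of contraceptive effect.
- **The planned sensitivity analysis would remove most pregnancies, and late attenders are assessed.** Partly so. That analysis is not primary, need not remove a woman who conceives on her allocated method, and comes with no scheduled month-6 test.
- **The analysis plan, not shown here, may handle this.** It may. But the protocol already defines the primary set as all with data, so an analysis plan that left these samples out would depart from it.

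A reader might go further and infer that a single pregnancy is bound to move an arm mean by the whole 35 pmol/L, ruin the power, or create a spurious difference. The documents do not support that. A shift of 35 needs an assumed value of at least 7,871 pmol/L at 221 per arm; the loss of power depends on the arm and the scale; and one outlier inflates the SE along with the mean, so the false-positive rate stays at about 5% or below.

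**Conclusion.** The point holds as a gap in how a primary outcome is defined. Sections 5.9 and 8.2 together place hormone samples drawn in pregnancy in the primary estradiol comparison and in the progesterone, SHBG and testosterone comparisons, and nothing scheduled at month 6 identifies them.

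Its size is conditional on assumed pregnancy values and on the analysis scale. Untransformed, a single pregnancy can leave the comparison nearly intact or remove its power, depending on the value and on which arm it falls in. On a log scale the cost is small for one pregnancy and becomes material only with several in the same arm. The stated sample sizes are sound and are not in question.

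**What to change.** - Keep pregnant women in follow-up and in all other outcomes, as section 5.9 intends.
- In section 5.8.4 and Table 2, add a pregnancy test on the urine already collected at month 6 and at month 6 plus 7 days, so that affected samples are identified in both arms alike.
- In section 8.2, fix a log scale for estradiol in advance.
- In section 8.2, state that hormone values drawn while pregnant are left out of the estradiol, progesterone, SHBG and testosterone comparisons, with the number left out shown by arm.
- Add a rank-based sensitivity analysis of the hormone outcomes that includes every sample.

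The cost is wording plus a urine strip per visit. The downside is a few post-randomisation exclusions, which could differ by arm; the counts by arm and the all-sample analysis let a reader judge whether they matter.

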#### **5.10 Criteria for discontinuation of the study**

An interim analysis will be performed by the statistical team and reviewed by the DSMB after 50% of women have completed the study. If the DSMB feels the data confirms significant harm or benefit of one of the study arms and recommends discontinuation of the study, enrolment will stop.

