#### **5. Study design**

This will be a 2-arm, multicenter randomised clinical trial where one group will be allocated to NET-EN use and the other to DMPA. The group allocated to NET-EN will be the treatment group and those allocated to DMPA will be the comparison group, as the majority of women

in the research settings use DMPA. The follow up period will be a minimum of 7 months, and pending funding up to 18 months.

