### **5.1 Methods and study procedures :**

The study design, procedures, inclusion and exclusion criteria, randomization procedures, follow up and data management are outlined below.

Biological samples will be collected at baseline, 6 months and 6 months 7 days to measure differences between women allocated to NET-EN versus DMPA in biological parameters relevant to HIV acquisition risk. Sample size: 520 participants

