## **5.5 Sampling and allocation**

The anticipated recruitment proportions will be 50% per site. Recruitment will continue at both sites until the total sample size is reached.

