### *Feasibility of recruiting necessary sample size*

Effective Care Research Unit has access to 18 primary health care centers where recruitment will take place. MatCH Research Unit has access to a large family planning clinic in Ethekwini, Kwazulu Natal.

We estimate recruitment for the 2 sites should be at least 40 per week, with completion in 12 weeks.

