### **8.3 Study timeline**

Ethical approval of protocol: 2 months

Development of the manual of procedures: 1 month

Administrative and organizational arrangements at sites: 1 month

Training for research staff: 1 month

Recruitment: 4 months

Follow-up: 7 months, pending funding 12-18 months

Data cleaning and analysis and manuscript: 3 months

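### The only interim analysis falls about five months after enrolment has closed, so its one stated consequence, ending enrolment, cannot take effect

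*Protocol*

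**What the plan says.** Section 5.10 of the protocol holds the only rule for stopping the study early. It sets one look: "An interim analysis will be performed by the statistical team and reviewed by the DSMB after 50% of women have completed the study". The criterion is a committee judgement: "If the DSMB feels the data confirms significant harm or benefit of one of the study arms". The consequence is that if the committee "recommends discontinuation of the study, enrolment will stop". The section says nothing about women already enrolled and still in follow-up.

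The schedule is given elsewhere in the protocol:

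- Section 5.1: "Sample size: 520 participants".
- Section 5.5: "Recruitment will continue at both sites until the total sample size is reached".
- Section 5.6, on feasibility: "We estimate recruitment for the 2 sites should be at least 40 per week, with completion in 12 weeks".
- Section 8.3: "Recruitment: 4 months".
- Section 5: "The follow up period will be a minimum of 7 months, and pending funding up to 18 months".

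Section 5.6 sizes both primary outcomes, BDI-II and serum estradiol, for a single comparison at 95% certainty and 80% power.

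**The concern.** Recruitment is short and follow-up is long. A look triggered by completion of follow-up in half the women must therefore come after the last woman has been randomised. An ethics committee or monitoring committee reading section 5.10 would take it as a means of limiting how many women are exposed if one arm looks worse. If it cannot do that, the protocol describes a protection that this rule does not give. It also leaves open what the committee could recommend at the time it actually sees the data.

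A second, smaller matter is the standard for stopping. The section refers to significant harm or benefit but cites no bound. Because benefit is included, the look could be taken as an efficacy test, and the sample size makes no allowance for one.

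**Working it through.** **The plan's own figures.** For two means, n per group = 2 × [SD × (1.960 + 0.842) / difference]².

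- Depression: SD 7.5 and difference 2 give 220.7, so 221. Then 221 / 0.85 = 260.
- Estradiol: SD 119 and difference 35 give 181.5, against 181 stated. Then 181 / 0.85 = 213.

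Both reproduce within rounding at a full two-sided 5% with no interim allowance. The total is 2 × 260 = 520.

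**When the look falls.** Let T be the recruitment period and F the follow-up per woman, both in months. With even accrual:

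- the 260th woman enters at T/2;
- the look falls at T/2 + F;
- enrolment closes at T;
- the gap after closure is F − T/2.

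Twelve weeks is 12 / (52/12) = 2.77 months.

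| Recruitment | Completion counted at | Look at month | Enrolment closes at month | Gap (months) |
|---|---|---|---|---|
| 12 weeks | 6 months | 7.4 | 2.8 | 4.6 |
| 4 months | 6 months | 8.0 | 4.0 | 4.0 |
| 12 weeks | 7 months | 8.4 | 2.8 | 5.6 |
| 4 months | 7 months | 9.0 | 4.0 | 5.0 |
| 12 weeks | 18 months | 19.4 | 2.8 | 16.6 |
| 4 months | 18 months | 20.0 | 4.0 | 16.0 |

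Counting completion at month 6 is the reading most favourable to the plan, and the gap is still at least 4 months. If 50% means 260 actual completers, loss to follow-up only delays the look.

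**What would make the rule work.** The gap reaches zero when T = 2F. With 7-month follow-up, recruitment would have to last more than 14 months, that is, fewer than 520 / (14 × 52/12) = 8.6 women per week against the planned 40 or more. With completion at month 6 it would have to last more than 12 months.

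**What is left to act on at the look.** With 7-month follow-up the last woman completes T/2 = 1.4 to 2.0 months after the look. The share of women already past month 6 is (T/2 + 1)/T = 0.5 + 1/T, which is 75% (4 months) to 86% (12 weeks). About 130 to 72 of the 520 are still short of month 6.

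**Type I error, conditional.** Suppose a primary outcome is tested at |Z| > 1.96 at the look and again at the end, and a crossing at either counts as a finding. At information fraction 0.5 the two statistics have correlation √0.5 = 0.707.

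- One outcome: P(|Z₁| > 1.96 or |Z₂| > 1.96) = 0.083. If data from women past month 6 were also used, so that the fraction is 0.75, it is 0.073.
- Two outcomes, taken as independent: 1 − (1 − 0.0831)² = 0.159. Without any interim it is already 1 − 0.95² = 0.0975, so the look would add about 6 percentage points.
- Haybittle-Peto, p < 0.001 at the look and 0.05 at the end: 0.0502 for one outcome.

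**The case against.** The timing arithmetic is hard to dispute, but several stronger readings would go too far.

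- **That women are unmonitored during enrolment.** The protocol does not support this. Section 12.2 sends serious adverse events to an independent committee and to the ethics committees, and section 5.8.5 gives participants a 24-hour number for reporting adverse events. What fails is one stopping rule, not safety oversight.
- **That the type I error is inflated as the plan stands.** Section 5.10 sets no 5% threshold and does not name the outcomes to be examined; harm or benefit could refer to safety events. A bound may stand in a statistical analysis plan or committee charter that is not shown, and its absence from the protocol is not an error. Moreover, if the look changes nothing and every woman continues, the final test on the full data keeps its 5%. Inflation needs an interim claim or an early end to the comparison.
- **That 16% is the price of the interim.** Most of that figure, 9.75%, comes from having two primary outcomes each tested at 5%.
- **That the committee should review HIV infections and pregnancies during enrolment.** Under section 5.8.4, study HIV testing after baseline starts at month 6 and the scheduled pregnancy test is at 12 to 18 months. Section 5.7.2 adds pregnancy assessment only for late injections. The recruitment window would hold almost no such data.
- **That 40 per week for 12 weeks gives 480 rather than 520.** Section 5.6 gives 40 as a minimum; 520 / 12 = 43.3 per week is compatible with it.

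All of these limits stand. None of them makes the stated consequence of the look achievable.

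**Conclusion.** The point holds on timing. On the planned schedule the look comes 5.0 to 5.6 months after enrolment has closed. The gap is 4.0 to 4.6 months if completion is counted at month 6, and 16.0 to 16.6 months with 18-month follow-up. The number of enrolments the rule can prevent is zero. This assumes even accrual at roughly the planned pace; only an overrun from 3 or 4 months to more than 14 (more than 12 on the month-6 reading) would reverse it.

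The error-rate point is conditional. It would be about 8.3% per outcome, and about 16% against 9.75% across two independent primary outcomes, only if an unadjusted 5% were used at both analyses and an interim crossing led to a claim. What the protocol text itself gets wrong is to rest the decision on what the committee feels is significant, without pointing to any criterion.

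This should be fixed, but it does not undermine the trial: the sample size reproduces and the planned final analysis is not shown to be wrong.

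**What to change.** Reconcile section 5.10 with sections 5, 5.6 and 8.3, in one of two ways:

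1. Schedule a committee review inside the 12- to 16-week recruitment window, limited to data that accrue then: adverse events, serious adverse events and early discontinuations. A recommendation to stop enrolment could then take effect.
2. Keep the look at 50% completion, and state what a recommendation to stop would change once enrolment is closed.

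If a comparative look at 50% completion is kept, replace the subjective criterion with a pre-specified strict bound, or a reference to where one is set. Haybittle-Peto at p<0.001 is suitable: overall error is 5.02%, the final test stays at 5%, and the sample size is unaffected. Otherwise, state that the two primary outcomes are tested only once, at the end.

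The cost is wording in the protocol and the committee's charter, plus one committee review if the first option is taken. It needs no more participants and no new tests. It should be done before the first enrolment, because the window in which a review can matter lasts only 3 to 4 months.
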